### 7.1.3.c Two-tailed versus One-tailed

Despite the fact that the diaphragm is unlike some candidate microbicides whose mechanism of action is to break down cell walls of both HIV and the cervical epithelium, the possibility remains that diaphragm use may be associated with increased infection risk via unknown mechanisms. For this reason, we felt that a two-tailed test would be most appropriate.

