**HPV sample collection:** At the enrollment visit, after the cytology sample is taken, the cervix and endocervix will be swabbed under direct visualization with a Dacron swab and stored in Sample Transport Medium (Digene Diagnostics, [name]) at 40C.. At follow-up visits, participants will be instructed in the technique of self-sampling and these samples will be stored in specimen transport medium as stated above. At the 12 month follow-up visit, a clinician-collected swab will be collected in addition to the self-collected swab. At study exit, a final clinician-collected swab will be obtained under direct visualization at the time of pelvic examination. Study exit will vary from 12 to 24 months depending on time of enrollment. Samples will be shipped to UCSF with cold packs for analysis in the laboratory of [name] by PCR using MY09/11 primers (see below). In addition, quantification of HPV levels will be performed by real-time PCR in HPV-positive samples from all women who sero-convert to HIV and a matched sample of controls who do not sero-convert. These will be reported as viral loads. Currently [name] laboratory has PCR primers and probes for quantitative PCR in HPV 16, 18 and 33-positive samples, and is developing assays for the remaining high risk HPV types.

**Secondary study outcome: Cervical dysplasia, biopsy-confirmed.** Women with abnormal Pap tests interpreted as AGUS, HSIL, adenocarcinoma in situ and cancer will be referred for immediate colposcopy. Women with Pap results of ASCUS or LSIL will undergo a repeat Pap smear after 6 months. If the results indicate ASCUS or worse, she will be referred for colposcopy. At the time of the exit Pap test, the threshold for referral will remain the same as at previous visits (cytologic abnormalities of AGUS, HSIL or worse). Women with exit Pap results of ASCUS or LSIL will be counseled and referred to local clinics for repeat Pap smears 6 months later. Colposcopists will be blinded to the arm of the study to which participants have been randomized. Women with colposcopic abnormalities will undergo diagnostic biopsies, and those with cervical intraepithelial neoplasia (CIN) 2 or 3 will undergo loop electrosurgical excision procedure. Women found to have cancer will be referred for cancer treatment. Histological analyses of biopsy and loop specimens will be performed in Zimbabwe. All colposcopic and histological data will be entered on a case report form and transferred to UCSF.

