**Statistical power.** For study aims #1-3, we calculated minimal detectable relative hazards for the main study outcomes based on the sample size of 2,200 enrollees with a 10% loss-to-follow-up rate, a power of 80% and a significance level of 5% (one-tailed alpha=0.05) using the log-rank test. We chose one-sided tests for this analysis since we do not believe that diaphragms increase risk of HPV outcomes. We performed analyses over a range of plausible prevalence rates of HPV (up to 40% for all types and as low as 20% for high-risk types) and evaluation periods (12 to 24 months). Prior studies of Zimbabwean sero-negative women have indicated a prevalence of HR HPV types of 28% 64. We assumed an annual HR HPV incidence rate of 8% and an annual clearance of 65% in the non-diaphragm arm based on studies from a high-risk area of Brazil 65. The prevalence of cytologic abnormalities was estimated at 15% and incidence at 10% per year in this high-risk population in the non-diaphragm arm. High-grade cervical intraepithelial neoplasia (CIN 2 or worse) prevalence was estimated at 5.9% based on a prior cross-sectional study in Zimbabwe 64. Assuming a cytology sensitivity of 62% 64 and an annual incidence rate of 0.5%, we estimated a prevalence of CIN 2 or worse of 3% by the end of the study in the non-diaphragm arm. For study aim #4, we assumed that 88 women would sero-convert to HIV-positive over the course of the study. We determined the minimal detectable odds ratios for a range of prevalence rates of predictors (e.g., HPV) at 80% power and one-tailed alpha of 0.05.

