Table 1 details all power analyses for study aims #1-3. Under a variety of assumptions, we will have power to detect 16-37% reductions in incidence and persistence of HPV between the diaphragm group and the non-diaphragm group. We will also have power to detect at least a 26% reduction in incidence of cytological abnormalities. We will have less power to be able to detect differences in biopsy-proven CIN 2 or worse (a secondary study aim): a minimum 63% reduction with diaphragm use must be demonstrable for us to be able to detect a statistically significant effect. For study aim #4, we will have adequate power to detect differences in HPV prevalence between sero-converters (cases) and non-sero-converters (controls) if control prevalence rates are 20-40% and cases have at least 2.2 times the prevalence of HPV (Table 2). We believe that we will have adequate power for this analysis; a prior study, for example, has shown that in Zimbabwean women, the prevalence of HR HPV types is over two-fold greater in HIV-positive women (64%) compared to HIV-negative women (28%) 64. Our main hypothesis for study aim #4 involves evaluating a variety of predictors with various prevalence rates (e.g., all HPV types, low-risk, types, high-risk types), and we will have similar power to detect differences for other predictors in this range.

**Table 1:** Least detectable hazard ratios for various HPV-related outcomes over time assuming a sample size of 2,200 enrollees with a 10% loss-to-follow-up rate, a power of 80% and a one-tailed alpha=0.05)

| **Study Aim** | **Outcome** | **Baseline prevalence** | **Observation period (months)** | **Least detectable Relative Hazard** |
| --- | --- | --- | --- | --- |
| **#1** | **HPV incidence**  All types  High-risk types |  | | |
| 40% | 12 | 0.63 |
| 20% | 24 | 0.74 |
| **#2** | **HPV persistence**  All types  High-risk types |  | | |
| 40% | 12 | 0.77 |
| 20% | 24 | 0.84 |
| **#3** | **Cytologic abnormality incidence** | 15% | 24 | 0.74 |
| **Secondary** | **Cervical intraepithelial neoplasia incidence** | 4% | 24 | 0.37 |

**Table 2:** Study aim #4 power: least detectable odds ratios for risk factor prevalences of 10-40% assuming 88 sero-converters and 2,112 non-sero-converters (power=80%, one-tailed alpha=0.05)

| **Risk factor prevalence (e.g., HPV)** | **Least Detectable Odds Ratio** |
| --- | --- |
| 10% | 2.8 |
|  |  |
| 20% | 2.3 |
|  |  |
| 30% | 2.2 |
| 40% | 2.2 |

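### HPV sub-study Table 1: the high-risk persistence (0.84) and high-risk incidence (0.74) rows do not follow from the sub-study's own inputs, and the 24-month rows ignore exit at 12 to 24 months

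*Protocol*

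**What the plan says.** The paragraph on statistical power in Appendix 16.2 gives least detectable relative hazards "based on the sample size of 2,200 enrollees with a 10% loss-to-follow-up rate", with "a power of 80% and a significance level of 5% (one-tailed alpha=0.05) using the log-rank test". It adds: "We assumed an annual HR HPV incidence rate of 8% and an annual clearance of 65% in the non-diaphragm arm". For cytologic abnormalities it takes 15% prevalence and 10% annual incidence.

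The specific aims restrict persistence to women who are HPV-positive at enrollment. The statistical methods paragraph analyses persistence as clearance among those women.

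Table 1 has six rows. Four use 24 months: high-risk incidence (20% prevalence, 0.74), high-risk persistence (20%, 0.84), cytology (15%, 0.74) and CIN (4%, 0.37). Two use 12 months: all-type incidence (40%, 0.63) and all-type persistence (40%, 0.77). The text sums up the HPV rows as "we will have power to detect 16-37% reductions in incidence and persistence of HPV between the diaphragm group and the non-diaphragm group", and gives at least 26% for cytology.

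On follow-up, the paragraph on HPV sample collection says "Study exit will vary from 12 to 24 months depending on time of enrollment". The note under Chart A agrees, and the main Study Summary (section 2) gives an 18-month average.

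On sidedness, the sub-study says "We chose one-sided tests for this analysis since we do not believe that diaphragms increase risk of HPV outcomes".

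**The concern.** The persistence row asks for more events than there are women who can have one. Each woman positive at enrollment contributes at most one clearance to a by-woman log-rank comparison, so the number at risk caps the events. The high-risk incidence row is also more favourable than its stated rate allows. The 24-month rows add follow-up that many women will not have.

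Persistence and incidence are numbered aims of the sub-study, and its limitations section expects adequate power for the main hypotheses. If the table stands, a null result on high-risk persistence would be read as evidence against a reduction of about 16%, when power for that effect is roughly one half or less.

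**Working it through.** **Inputs.** N = 2,200, 10% loss, 80% power, one-sided 5%, log-rank, and the rates above, all from Appendix 16.2. Arms are 1:1, as in the main trial. Loss is taken as removing 10% of the women at risk. Annual figures are read both as a hazard h and as a one-year risk, where h = -ln(1 - risk).

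**Formulas.** Events needed: D = 4(1.645 + 0.842)² / (ln HR)². Events expected: n × ½[(1 - e^(-ht)) + (1 - e^(-HR·h·t))]. The least detectable HR is the value at which the two agree.

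**Rows that reproduce.**
- Cytology: n = 2,200 × 0.85 × 0.9 = 1,683, h = 0.10, 2 years. Result 0.738 (0.744 if 10% is a risk), against 0.74 stated.
- All-type persistence: n = 2,200 × 0.40 × 0.9 = 792, h = 0.65, 1 year. Result 0.765 (0.797 if 65% is a risk), against 0.77 stated.

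**High-risk persistence, stated 0.84.**
- Needed: 4 × 2.487² / (ln 0.84)² = 814 clearances.
- At risk: 2,200 × 0.20 = 440; after loss, 396.
- If every woman cleared, the least detectable HR would be exp(-2 × 2.487/√396) = 0.779, or 0.789 with all 440. Power at 0.84 would be 54% or 57%.
- At 65% per year over 24 months with 396 women, the result depends on how 65% is read and on whether the diaphragm slows clearance (HR below 1) or speeds it (reported as 1/HR):

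| 65% read as | Slower clearance | Faster clearance |
|---|---|---|
| Hazard 0.65 | 0.737 | 0.753 |
| Annual risk (h = 1.05) | 0.761 | 0.769 |

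- The range is therefore 0.74-0.77, and power at 0.84 is about 42-50%.
- At the 28% high-risk prevalence that the text also cites, n = 2,200 × 0.28 × 0.9 = 554 and the one-sided 24-month value is 0.77-0.80. Even 40% prevalence leaves 792 women after loss, fewer than 814.

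**High-risk incidence, stated 0.74.**
- Needed: 4 × 2.487² / (ln 0.74)² = 273 events.
- At risk: 2,200 × 0.80 × 0.9 = 1,584, or 792 per arm.
- Expected at HR 0.74: 792(1 - e^(-0.16)) + 792(1 - e^(-0.1184)) = 117.1 + 88.4 = 206 (214 if 8% is a risk).
- Least detectable HR: 0.704-0.710. Leaving out the 10% loss gives 0.718-0.723, still short of 0.74.

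**Follow-up.** The documents give the range and the mean, not the distribution. I assume exit uniform over 12 to 24 months (mean 18), which replaces e^(-ht) by (e^(-h) - e^(-2h))/h.

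| Row | Stated | 24 months for all, one-sided | 12-24 months, one-sided | 12-24 months, two-sided |
|---|---|---|---|---|
| High-risk incidence | 0.74 | 0.70-0.71 | 0.67 | 0.63-0.64 |
| High-risk persistence | 0.84 | 0.74-0.77 | 0.72-0.76 | 0.68-0.73 |
| Cytology | 0.74 | 0.74 | 0.70-0.71 | 0.67-0.68 |

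**Not checked.** The text gives no all-type incidence rate, so the 0.63 row, and with it the 37% end of the range, cannot be tested. The CIN row comes close (about 0.36 against 0.37) only if I assume that the 3% end-of-study prevalence is multiplied by the 62% cytology sensitivity. I offer no replacement for it.

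**The case against.** **The 0.84 may be a labelling slip.** The summary sentence covers several assumptions, and the text examined prevalence up to 40% and periods up to 24 months. With 40% prevalence, 24 months, 65% as an annual risk and faster clearance, the detectable value is 0.838 without loss and 0.830 with it. That is a plausible origin. But the row is printed as 20%, the table declares 10% loss, and the text attaches 40% to all types, not to high-risk types. Either the label or the value must change.

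**Other routes to 0.84.** A ratio of 24-month clearance proportions (hazard 0.65, 198 per arm) gives 0.839. That is not a relative hazard, and the same reading gives 0.82, not 0.77, for the other persistence row. Counting several HPV types or repeat clearances per woman would raise the events, but Table 1 rests on a log-rank test and the aims define persistence by woman.

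**Stronger readings that do not hold.**
- A reader might infer that the whole table assumes 24 months. The 0.63 and 0.77 rows use 12 months, the minimum planned follow-up.
- A reader might count the one-sided alpha as part of the error, or say that section 7.1.3.c forbids it. The choice is declared, reasoned and labelled in the captions. Section 7.1.3.c concerns the HIV sample size, where the protocol says "the possibility remains that diaphragm use may be associated with increased infection risk via unknown mechanisms" and concludes "For this reason, we felt that a two-tailed test would be most appropriate". The two lines of reasoning about the same device sit uneasily together, which merits a design remark and no more.
- A reader might infer that harm could not be seen. One-sidedness appears only in the power text; the HPV analysis paragraph plans 95% confidence intervals, which would show it.

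**Consequence.** The sub-study's size is set by the Zimbabwe cohort, and nothing in the HIV endpoint depends on this table. That is true and limits the weight of the point, but the stated power is still wrong.

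**Conclusion.** The point holds for two rows as arithmetic and for four rows on follow-up. High-risk persistence at 0.84 is unattainable on its printed inputs: 814 clearances are needed from at most 440 women, and the supported value is about 0.74-0.77. High-risk incidence at 0.74 is optimistic: 273 events are needed and about 206 expected, which supports 0.70-0.71. The high-risk incidence, high-risk persistence, cytology and CIN rows also assume 24 months for every woman, against planned exit at 12 to 24 months.

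The first two conclusions use only the sub-study's own figures and a formula that reproduces two other rows. The follow-up values rest on my assumption of uniform exit. The two-sided values illustrate the design remark and are not corrections.

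**What to change.** 1. Correct the high-risk persistence and high-risk incidence rows of Table 1. State whether 65% is a hazard or an annual risk, and in which direction the relative hazard for clearance is expressed.
2. Recompute the four 24-month rows for exit at 12 to 24 months, and state the exit distribution assumed.
3. Restate the summary, one-sided as declared: about 24-28% for high-risk persistence in place of the 16%, about 33% for high-risk incidence, and about 29-30% for cytology in place of 26%. The smallest detectable reduction in the HPV rows would then be the 23% of the unchanged all-type persistence row (0.77 at 12 months).
4. Give the all-type incidence rate behind the 0.63 row so that the 37% can be checked.
5. Separately, either explain why the two-tailed reasoning of section 7.1.3.c does not carry over to HPV, or show two-sided values beside the one-sided ones.

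The cost is one table and a few sentences, and less favourable stated power. Enrollment, visits and testing do not change.

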# 7 Accrual, Follow-up, and Sample Size

## 7.1 Primary Endpoint

**7.1.1 Required sample size**

Sample size calculations are made by comparing HIV incidence rates between study arms using a log rank test stratified by study site and using approximate methods described by Lachin and Foulkes. 26We initially assumed that participants will be recruited over a period of 2 years, that the duration of the study would be 3 years, and that annual HIV incidence in the non-diaphragm arm (control group) would be approximately 4%, 5% and 3.5%at the Harare, Durban, and Johannesburg sites respectively. We further assumed that these sites would contribute 49%, 29%, and 22% of the total sample respectively and that discontinuation rates, including lost to follow up and true discontinuations, would not exceed approximately 7% per year at all sites or a total of approximately 20% over the three-years field implementation period. With these assumptions we required a total of 4500 women to have 90% power to detect a 33% treatment-related reduction in incidence as significant at the 5% level, assuming a two-sided alternative. This sample size and the assumption of constant rates of recruitment and censoring implies that approximately 4000 woman years of follow-up will be required per arm to detect a treatment-related reduction in incidence of 33%. This corresponds to a total of approximately 293 total serconversions in both arms combined. The following table presents enrollment goals and expected numbers of seroconversions by site.

**Table 4***: Approximate numbers of women to be enrolled to reach required number (293) seroconversions. We assume approximately 20% discontinuation rate at each site over the entire study period.*

|  | **Enrolled** | **Estimated annual incidence (overall)** | **Minimum estimated**  **Infections** |
| --- | --- | --- | --- |
| Harare | 2200 | 4% | 134 |
| Durban | 1300 | 5.0% | 99 |
| Johannesburg | 1000 | 3.5% | 60 |
| **Total** | **4500** | **~4.0%** | **293** |

If incidence is actually higher than assumed here, the diaphragm actually confers more than 33% protection, or the discontinuation rate is lower, it may be possible to end the study early. This decision will be made via stopping rules that will be considered during the interim analysis conducted by our DSMB (section 12.6. below).

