All HPV tests will be reported as positive for high-risk types, positive for low-risk types, positive for both, or negative for both. High-risk types will be defined as the presence of types 16, 18, 26, 31, 33, 35, 39, 45, 51, 52, 53, 56, 58, 59, 66, 68 and 73 33. Low-risk types will be defined as 6, 11, 40, 42, 54, 61, 70 and 72 33. If the beta-globin control is positive but no HPV is detected, the specimen will be considered “negative.”

**Statistical methods and analyses.** HPV prevalence will be estimated as the observed proportion positive, and associated precision summarized using a 95% exact binomial confidence interval. Incidence of HPV during follow-up will be investigated using survival analysis techniques appropriate for grouped or discrete time outcomes to account for intervals between visits. Initial analyses will include incidence over follow-up of particular types or groups of types among women confirmed to be negative at the baseline visit and will be summarized using life table estimates and 95% confidence intervals. We will use a similar approach in investigating persistence by examining differences in clearance among prevalent positives in both randomized groups. To accommodate repeated episodes of infection and clearance for high-risk types, we will also investigate the use of Markov models for panel data, taking negative and positive HPV tests at study visits as the observed states. These models will allow all available follow-up data to be used, provide direct estimates of the transition probabilities between positive and negative states and allow time-varying risk factors to be investigated using a proportional hazards model similar to those described above. Outcomes of viral load and cytologic and histologic abnormalities will be analyzed similarly.

For study aim #4, we will compare the prevalence rates of HPV (e.g., all HPV types, low-risk, types, high-risk types) between sero-converters and non-sero-converters using matched analysis controlled for confounders. We will separately evaluate the potential association between sero-conversion and HPV viral load using a 3-to-1 control-to-case ratio rather than the entire cohort of non-sero-converters since this assay is relatively expensive to perform.

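### HPV sub-study, Aim 4: the detectable odds ratios in Table 2 do not follow from the table's own caption, and the text misreads them as ratios of prevalence

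*Protocol*

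**What the plan says.** Aim 4 asks whether HPV infection raises the risk of acquiring HIV. Four places in the protocol bear on its power.

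- **Appendix 16.2, Statistical power.** The case count is fixed: "For study aim #4, we assumed that 88 women would sero-convert to HIV-positive over the course of the study". Detectable odds ratios are then derived "at 80% power and one-tailed alpha of 0.05".
- **Appendix 16.2, Table 2.** The caption gives the group sizes, "assuming 88 sero-converters and 2,112 non-sero-converters". The printed odds ratios are 2.8, 2.3, 2.2 and 2.2 at prevalences of 10, 20, 30 and 40%. The text before the tables calls power adequate "if control prevalence rates are 20-40% and cases have at least 2.2 times the prevalence of HPV (Table 2"). It supports this with a cross-sectional study in which 64% of HIV-positive and 28% of HIV-negative women carried high-risk HPV.
- **Appendix 16.2, Statistical methods and analyses.** HPV prevalence is compared between seroconverters and non-seroconverters "using matched analysis controlled for confounders". A 3-to-1 ratio is used for viral load in place of the full cohort, which implies that the prevalence comparison uses the full cohort. No matching ratio is given for it.
- **Section 7.1.1, Table 4.** The row for the same site reads "Harare | 2200 | 4% | 134": 2,200 women, 4% a year, 134 infections.

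**The concern.** The caption fixes every input of a standard two-group calculation, so the table can be checked directly, and it fails the check. The summary sentence then moves from odds ratios to ratios of prevalence. With exposures as common as 20 to 40% the two scales differ greatly, so the sentence misdescribes even the table as printed. A reader deciding whether Aim 4 is worth its laboratory cost, or later interpreting a null result, would take away the wrong detectable effect.

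Two secondary points feed the same judgement. The case count does not agree with the main protocol. The evidence offered for a large effect comes from women who already had HIV, whereas the aim concerns HPV before HIV.

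**Working it through.** **Inputs.** 88 cases, 2,112 controls, 80% power and one-sided alpha 0.05 (z = 1.645), all from the Table 2 caption. Control prevalence p0 is 10, 20, 30 or 40%.

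**Formulae.** Case prevalence at a given odds ratio: p1 = p0·OR / (1 − p0 + p0·OR). Power = Φ{[p1 − p0 − 1.645·√(p̄(1 − p̄)(1/88 + 1/2112))] / √(p1(1 − p1)/88 + p0(1 − p0)/2112)}, where p̄ is the pooled prevalence. The detectable odds ratio is the one that gives power 0.80.

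**Worked row, p0 = 20%.**
- At OR 1.835: p1 = 0.367/1.167 = 0.3145, p̄ = 0.2046, null SE = 0.0439, alternative SE = 0.0503. Then (0.1145 − 1.645 × 0.0439)/0.0503 = 0.84, which is 80% power.
- At the printed OR of 2.3: p1 = 0.46/1.26 = 0.365, null SE = 0.0440, alternative SE = 0.0521. Then (0.1651 − 0.0725)/0.0521 = 1.78, which is 96% power.

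**All rows.**

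| Control prevalence | Printed OR | OR from caption (88 v 2,112) | Power of 88 v 2,112 at printed OR | OR for 88 v 88 | Case prevalence at printed OR | Prevalence ratio at printed OR |
|---|---|---|---|---|---|---|
| 10% | 2.8 | 2.11 | 96% | 2.84 | 23.7% | 2.37 |
| 20% | 2.3 | 1.84 | 96% | 2.33 | 36.5% | 1.83 |
| 30% | 2.2 | 1.74 | 97% | 2.17 | 48.5% | 1.62 |
| 40% | 2.2 | 1.72 | 98% | 2.13 | 59.5% | 1.49 |

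The plan's figures are not reproduced from its caption. Testing two-sided gives 2.27, 1.96, 1.86 and 1.84, and allowing 10% loss (79 v 1,901, one-sided) gives 2.19, 1.89, 1.79 and 1.77, so neither explains the gap. Three controls per case (88 v 264, one-sided) give 2.35, 1.99, 1.88 and 1.85. Equal groups of 88 come close, matching three rows to one decimal and missing the fourth (2.13 against 2.2).

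**Scale.** A true 2.2-fold prevalence at 20, 30 and 40% means 44, 66 and 88% of cases, which are odds ratios of 3.1, 4.5 and 11.0. At 40%: (0.88/0.12)/(0.40/0.60) = 11. The 20% row also prints 2.3, not 2.2.

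**Case count.** 2,200 × 0.04 = 88, which is one year of follow-up. Table 4's 134 is 134/88 = 1.52 years per woman, in line with the 18-month average follow-up in Section 2. With 134 v 2,066, one-sided, the detectable odds ratios would be 1.88, 1.66, 1.58 and 1.56.

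**Supporting evidence.** 64% against 28% is a prevalence ratio of 0.64/0.28 = 2.29 and an odds ratio of (0.64/0.36)/(0.28/0.72) = 4.57, measured in women already HIV-positive. The appendix's own background says that immunocompromised people are more likely to carry HPV, so the association could run from HIV to HPV.

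**The case against.** Five points can be made for the plan.

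1. **Origin of the table.** A reader might infer that it was computed for 88 against 88. The document does not say so, and that calculation misses the 40% row. Because the analysis is to control for confounders, an adjusted calculation is also possible: 88 v 2,112 with an unstated covariate R² of about 0.52 (variance inflation 1/0.48 = 2.08) gives 2.76, 2.33, 2.20 and 2.18, which round to all four printed values. This stands. The origin is unknown, and only the mismatch with the caption is established.
2. **Direction.** With 2,112 controls the error is conservative, and so is the lower case count. This stands too. Nothing here shows that Aim 4 is underpowered.
3. **Reverse causation.** A reader might infer that the analysis would attribute HPV caused by HIV to the opposite path. The documents do not support that. The aims section compares HIV acquisition by HPV status, all women are HIV-negative at enrollment when the first cervical swab is taken, and swabs follow quarterly. The methods are merely silent on which swab defines exposure.
4. **Case count.** The sub-study needs separate consent, so its seroconverters need not equal the Harare total. Hence 134 is not shown to be the right number. The two figures need reconciling.
5. **Test and model.** One-sided testing for Aim 4, or a model without lagged exposure, is a design choice. Neither is an error that this check establishes.

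None of this rescues the prevalence sentence, which is wrong however Table 2 was produced.

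**Conclusion.** The point holds in two firm parts. First, Table 2 does not follow from its caption: the stated inputs give odds ratios of about 2.1, 1.8, 1.7 and 1.7, not 2.8, 2.3, 2.2 and 2.2. Either the caption names the wrong control set, or an assumption is missing, or the values are wrong. If the full cohort is used, power is understated. Second, reading the table as a 2.2-fold prevalence is a scale error, since the printed values at 20 to 40% are prevalence ratios of about 1.8 to 1.5.

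The 88 against 134 discrepancy and the 64% against 28% support are real but secondary. The recomputation assumes an unadjusted comparison of two proportions with a pooled null variance. The matter is confined to one aim of a single-site sub-study and leaves the trial's primary analysis and sample size untouched.

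**What to change.** - State the control set and matching ratio for the prevalence comparison, and separately for viral load. Name any covariate adjustment assumed in the power calculation.
- Recompute Table 2 for that design, with a case count reconciled with Table 4 after allowing for sub-study consent.
- Replace the 2.2-fold statement with odds ratios shown beside the case and control prevalences they imply.
- Stop resting adequacy on the 64% against 28% comparison.
- State that HPV exposure is taken from a swab at or before the last HIV-negative visit.

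The cost is one recalculated table and a few sentences. No new samples or visits are needed, because the swabs are already scheduled.
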